## **ETHICAL CONSIDERATIONS**

The study protocol and forms will be submitted to the UCSF Committee on Human Research as well as the Centre Steering Committee, Scientific Steering Committee, and Ethical Review Board of KEMRI, the Kenya Medical Research Institute.

**Human Subjects Involvement and Characteristics:** The human subjects who will be involved in the proposed study will be HIV-positive women and men, as well as clinic staff, at the study health facilities in Suba, Kisumu East, Rongo and Migori Districts, Nyanza Province, Kenya. Clients of the FACES-supported clinics and clinic staff will be invited to participate in face-to-face surveys and interviews, each of which will take 30-45 minutes to complete. In addition, data will be abstracted from the patient records to measure contraceptive prevalence and pregnancy rates. It is necessary to include HIV-positive women and men in this study as they are the main beneficiaries of integrated family planning and HIV services and the effectiveness of this approach can only be appropriately judged based on their experiences and outcomes with integrated vs. non-integrated services. The research will be performed at health facilities in Suba, Kisumu East, Rongo and Migori Districts, Nyanza Province, Kenya, as a collaboration between colleagues from the Kenya Medical Research Institute (KEMRI), Family AIDS Care and Education Services (FACES) and UCSF and Ibis Reproductive Health. The collaborating institutions will be equally involved and support implementing the integrated or non-integrated services at the study health facilities, abstraction of data from patient records, developing the interview guides and informed consent forms, as well as participating in analysis, interpretation, and dissemination of the study findings.

**Sources of Materials:** Data on contraceptive prevalence and pregnancy rates will be abstracted from information normally obtained in patient records as a part of their regular HIV care. The form used to abstract the data will not include the woman's name or address. The form will include a patient study ID number and the client's medical record number in order to be able to track treatment and outcomes from her medical record over time. However, medical record numbers will not be entered into the study database, only the study ID numbers.

The baseline surveys with female and male clients will be filled out during a face-to-face interview after obtaining informed consent (see below). No identifying information will be

collected as part of the surveys, and the questionnaires will be labeled only with a study ID number that is not linked to the client's medical record.

For the open-ended interviews with clients and clinic staff, after obtaining permission from participants through an informed consent process (see below), the interviews will be audio-recorded. The recording will not be initiated until after the informed consent process is complete and any initial introductions that might include identifying information have been completed. The recording will not include the participant's name or any identifying information, only a study ID #. A separate form will be used to record information on the participant's socio-demographic characteristics (age, education, marital status, number of living children, employment, etc.) but will not include the participant's name, birth date, or specific identifying information, only the study ID #. Audio recordings will be transcribed (and translated into English if necessary) by persons who do not have access to identifying information on the participants.

**Potential Risks:** Potential risks to clients participating in the study include any social risks involved if information they reveal about their HIV status or other sensitive issues were to be disclosed outside of the research. Potential risks to clinic staff participating in the interviews include the above mentioned social risks, as well as a potential employment risk if negative information they reveal about their work environment or work practices were to be disclosed to their supervisors. Potential interview participants (both clients and clinics staff) will have the option of not participating in any part or the full interview, or refusing the audio-recording, without any adverse consequences for their medical treatment or employment.

### **Informed Consent:**

#### **Baseline and follow-up surveys with male and female clients**

Male and female clients will be invited to participate in the surveys (both baseline and follow-up) after they have completed their visit at the PSC site. They will be given information about the study and their rights as a part of the informed consent process. If they agree to participate, they will be asked to sign an informed consent form. As part of this informed consent process, potential participants will be informed of: (1) the purpose and methods of the study, (2) procedures to protect the confidentiality, (3) their rights to withdraw from the study at any time, (4) the fact that their participation or non-participation will not affect the medical care that they receive, and (5) persons to contact if they have any questions about the study after the completion of the interview. The participating clients will also be given a copy of the consent form to keep. This page will include names and phone numbers of persons to contact with any questions regarding the study. The consent form for clients participating in the surveys is included in Appendix C. The interviewer will also ask follow-up questions to ensure that the informed consent process has been well understood by the potential participant.

#### **Baseline and follow-up open-ended interviews with female and male clients**

A portion of clients who participate in the survey will be invited to participate in an additional open-ended interview. Before beginning the interview, informed consent will be obtained for the interview. The informed consent process for the interview will be identical to that of the survey with the addition of requesting permission to record the interview. If they refuse, audio recording will not be used; the interviewer will then take detailed notes during the interview. The consent form to be used with clients undergoing the open-ended interview is included in Appendix D.

#### **Baseline and follow-up interviews with clinic staff**

Health care workers in study facilities will be approached by the interviewer at a convenient time, either during their lunch break or before or after office hours. They will be given

information about the study and their rights as a part of the informed consent process, and if they agree to participate, they will be asked to sign an informed consent form. This consent form will explain that they will be asked to participate in a one-time face-to-face interview. As part of this informed consent process, potential participants will be informed of: (1) the purpose and methods of the study, (2) procedures to protect the confidentiality, (3) their rights to withdraw from the study at any time, (4) the fact that their participation or non-participation will not affect their employment at the study health facilities, and (5) persons to contact if they have any questions about the study after the completion of the interview. They will also be asked for permission to record the open-ended portion of the interview. If they refuse, audio recording will not be used; the interviewer will then take detailed notes during the interview. The participating clinic staff will also be given a copy of the consent form to keep. This page will include names and phone numbers of persons to contact with any questions regarding the study. The interviewer will also ask follow-up questions to ensure that the informed consent process has been well understood by the potential participant. The consent form to be used with clinic staff in this study is included in Appendix E. Clinic staff that are interviewed to collect cost data will not be asked to sign a consent form as this is standard for costing analyses.

### **Baseline and post-intervention site-based data collection**

Informed consent will be obtained from female clients age 18-45 and male clients age 18 and above to obtain permission to abstract data from their medical records at the FACES site. They will be given information about the study and their rights as a part of the informed consent process. If they agree to allow data abstraction from their medical record, they will be asked to sign an informed consent form. As part of this informed consent process, potential participants will be informed of: (1) the purpose and methods of the study, (2) procedures to protect the confidentiality, (3) their rights to withdraw from the study at any time, (4) the fact that their participation or non-participation will not affect the medical care that they receive, and (5) persons to contact if they have any questions about the study after the completion of the interview. The participating clients will also be given a copy of the consent form to keep. This page will include names and phone numbers of persons to contact with any questions regarding the study. The consent form for clients participating in the site-based data collection is included in Appendix F. The interviewer will also ask follow-up questions to ensure that the informed consent process has been well understood by the potential participant.

**Protection against risk:** Forms for abstraction of data on the care and outcomes of HIV-positive clients will not include names or addresses, only the client's medical record number and his or her study ID number. These forms will be kept in a locked cabinet at the research office in Suba District and no one outside of the core research team members will have access to these forms.

All interviews with clients and clinic staff will be conducted in a private room designated for this purpose at the study health facilities. No identifying information will be included on the audio recording of the interview. The form for recording socio-demographic characteristics of participants will not include the participant's name or other identifying information. Interview recordings, transcripts, and forms will be stored in a locked cabinet at the research office in Suba District and on a computer only accessible by core members of the research team. When these procedures are followed, it is highly unlikely that any of the information revealed by participants during the course of the interviews will be disclosed to anyone outside the research team. Given the small number of health care providers at some facilities, results will never be presented separately by facility, as that might identify specific participants. Results will only be presented by site type (sub-district hospital vs. dispensary) or by study group (integrated vs. non-integrated).

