## **STUDY DESIGN/METHODOLOGY**

### **Overview**

The study will have three parts. During the first part (3 months), baseline data on contraceptive prevalence and unintended pregnancy will be collected at 18 PSCs that are supported by the FACES program in Suba, Kisumu East, Rongo and Migori Districts. Also during this first part, information about knowledge, attitudes and practices related to family planning will be obtained from patients and from clinicians at the sites. During the second part (3 months), an intervention consisting of integrating family planning services will be designed and implemented at twelve of the 18 FACES-supported PSCs. We aim to utilize a 2:1 integration:control model, with delayed integration so as to gradually expand the integration of FP and HIV services throughout the 18 sites, while maintaining the ability to test hypotheses on the effects of integration on health outcomes. After collecting the baseline data, we plan to stratify the clinics into two categories based on the overall patient volume and differences in the structure of family planning provision, i.e., whether or not there is a specific MCH division providing family planning at the site or not. Randomization of sites will then occur among clinics in each of these strata, with a ratio of two intervention sites (integrated model) to one control site (family planning provided in the standard manner at the site). During the third and last part (9 months), data on contraceptive prevalence and unintended pregnancy will be collected from each of the 18 sites. At the end of part three, information about knowledge, attitudes and practices related to family planning again will be obtained from female patients and from clinicians at the sites. In addition, we will administer questionnaires assessing the acceptability of family planning services to patients, and in addition clinic staff will be answer a questionnaire assessing the feasibility of providing integrated family planning services.

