### **3. Part III: Post-intervention data collection (Months 7-15)**

#### **3.1. Post-intervention site-based data collection**

Over the following nine months, data on contraceptive prevalence, contraceptive methods used and pregnancy (including degree to which pregnancy was planned and desired) will be collected, as part of routine care, at the 18 sites (twelve intervention and six control sites) among women age 18-45 and men age 18 and older. Data will also be collected on whether contraceptive counseling was performed at each clinic visit. This information will be collected in the standardized clinic encounter form from all HIV-positive women and men at the time of each visit to the site. At each of the sites, a random sample of 10-15% of all charts will be reviewed during the post-intervention period to determine if the family planning module of the clinical encounter form is being filled out. A draft of the questions that will be used to collect the site-based data is included in Appendix A.

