### **ENDPOINTS**

**Primary Outcomes** (data abstracted from clinic encounter forms from all HIV-positive clients):

1. Contraceptive prevalence
  - a. Will compare post-intervention data from intervention sites to data collected over same time period from control sites
2. Pregnancy rate (number of pregnancies/number of unique clients seen during post-intervention data collection period) and percent of pregnancies that are unplanned
  - a. Will compare post-intervention data from intervention sites to data collected over same time period from control sites

**Secondary Outcomes** (data collected from KAP surveys and in-depth interviews):

1. Knowledge of contraceptive methods among HIV-positive clients
  - a. Will compare pre-intervention rates from baseline data to post-intervention data at intervention sites

- b. Will compare pre-intervention rates from baseline data to post-intervention data at control sites
  - c. Will compare post-intervention data from intervention sites to data collected over same time period from control sites
- 2. Knowledge of contraceptive methods among providers, including peer counselors, at HIV care and treatment centers
  - a. Will compare pre-intervention rates from baseline data to post-intervention data at intervention sites
  - b. Will compare pre-intervention rates from baseline data to post-intervention data at control sites
  - c. Will compare post-intervention data from intervention sites to data collected over same time period from control sites
- 3. Acceptability of family planning services
  - a. Will compare pre-intervention rates from baseline data to post-intervention data at intervention sites
  - b. Will compare pre-intervention rates from baseline data to post-intervention data at control sites
  - c. Will compare post-intervention data from intervention sites to data collected over same time period from control sites
- 4. Feasibility of providing family planning services at HIV care and treatment centers (data from post-intervention surveys of clinic staff)
- 5. Reproductive intentions of HIV-infected clients receiving care and treatment (data from baseline client surveys and in-depth interviews)

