## **LIMITATIONS**

### **Potential Design Pitfalls**

Non comparable sites: Government facilities in Suba, Kisumu East, Rongo and Migori Districts provide varying levels of care from basic outpatient dispensaries with minimal staff and facilities and services, to the district hospital with comprehensive diagnostic and treatment services including inpatient and outpatient facilities. Comparisons of facilities offering different levels of care would likely introduce confounding factors into the study outcomes. To avoid this potential confounding influence, we will perform an initial assessment of each of the possible sites and divide them into similar groups according to the number of clients served, the type of facility, the geographical location, and the type of HIV and family planning services currently available on site. We will group the sites into two strata based on this information; six intervention and three

control sites will be selected from each of the two strata. In addition, intra-cluster correlation is factored into our data analysis plan (see above section on statistical/analysis plan).

Non-uniform protocol implementation: We will train all health staff and paramedical staff in the standard operating procedure for each HIV care and treatment clinic, including the standard operating procedures for integration or non-integration of family planning services with HIV care and treatment. However, as in all settings, it is impossible to control for individual staff motivation. Therefore, it is possible that some sites will follow the protocol more stringently than others and that some sites will recruit patients more enthusiastically than others. With a randomized design the potential confounder of staff motivation should be evenly distributed in both the intervention and the control arms, thereby minimizing the problem of confounding influences.

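### The primary data are described as covering all HIV-positive clients but come only from those who consent, some of them after the site's arm is known, so selection into the comparison can differ by arm

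*Protocol*

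**What the plan says.** Two parts of the Protocol describe complete coverage. Endpoints gives the source of the primary outcomes as "data abstracted from clinic encounter forms from all HIV-positive clients". Section 3.1 says the information is "collected in the standardized clinic encounter form from all HIV-positive women and men at the time of each visit".

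The Informed Consent text on site-based data collection, which covers both the baseline and the post-intervention periods, sets a condition: "Informed consent will be obtained from female clients age 18-45 and male clients age 18 and above to obtain permission to abstract data". It continues: "If they agree to allow data abstraction from their medical record, they will be asked to sign an informed consent form".

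On timing, the Overview says "After collecting the baseline data, we plan to stratify the clinics into two categories", and then "Randomization of sites will then occur among clinics in each of these strata". Section 3.1 places the outcome data later: "Over the following nine months, data on contraceptive prevalence, contraceptive methods used and pregnancy" are gathered in months 7-15. Section 2.2 has intervention sites counsel at length and supply methods on site, while control sites generally refer.

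Under Potential Design Pitfalls the Protocol accepts that "some sites will recruit patients more enthusiastically than others". Its answer is that randomisation should spread staff motivation evenly over the arms.

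**The concern.** The analysed population is the consenting clients, not everyone seen. A client who consented in Part I did so before any site had an arm. A client first approached in months 7-15 is approached at a site whose arm is fixed and evident from the care given, and no blinding of clients, staff or consent-takers is described. Nothing limits the post-intervention comparison to Part I consenters; the pregnancy rate, for example, is defined over the unique clients seen in that period.

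If the arm changes who is approached or who signs, and that is related to contraceptive use, the difference in prevalence between arms is partly a difference in selection. Randomisation balances what exists before allocation. It does not balance approach or consent behaviour that arises afterwards in response to the arm. The intention-to-treat statement in the Data analysis plan classifies facilities whatever services women received; it does not deal with women absent for lack of consent. A test computed on consenters cannot detect the gap.

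**Working it through.** **The plan's own figure.** The Protocol gives no consent rate. Its sample size is not in dispute and supplies the scale: 22% v 30%, two-sided alpha 0.05, power 0.8, ICC 0.01, 12 v 6 sites, 140 women per site, 2,520 in total.

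- Two-proportion formula at 2:1, without continuity correction: 358 control women under individual randomisation.
- Design effect: 1 + (140 − 1) × 0.01 = 2.39.
- Total: 3 × 358 × 2.39 = 2,567, within 2% of 2,520. Power at 140 per site is 79.3%.

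**Room for selection.** Sample size considerations gives about 200 eligible women per site as a conservative figure and 333 as the average. A target of 140 is 140/200 = 70% to 140/333 = 42% of them. If sites work to that target, who is approached matters as well as who agrees.

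**Illustration of size.** Assumptions, none of them in the documents apart from the 22%:

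- True prevalence is 22% in both arms, so there is no effect.
- At control sites consent is unrelated to use.
- At intervention sites users consent with probability a and non-users with probability b.
- A share f of the analysed intervention women consents after allocation; the rest show 22%.

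Observed prevalence among post-allocation consenters = 0.22a / (0.22a + 0.78b). Spurious difference = f × (observed − 0.22).

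| a v b | Observed | f = 1 | f = 0.5 | f = 0.25 |
|---|---|---|---|---|
| 90% v 80% | 0.198/0.822 = 24.1% | 2.1 | 1.0 | 0.5 |
| 90% v 75% | 0.198/0.783 = 25.3% | 3.3 | 1.6 | 0.8 |
| 95% v 70% | 0.209/0.755 = 27.7% | 5.7 | 2.8 | 1.4 |

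The last three columns are percentage points, to be set against the 8 points the trial is sized to detect. If a = b the difference is zero. It is also zero if control sites have the same a, b and f.

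**Effect on the test.** With 840 control and 1,680 intervention women and design effect 2.39, the standard error for 22% v 24% is √[2.39 × (0.22 × 0.78/840 + 0.24 × 0.76/1680)] = 2.7 points. By the normal approximation, a spurious difference of 1 point raises the two-sided rejection rate from 5% to 6.6%, 2 points to 11%, and 4 points to 30.5%.

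**The case against.** The other side has several fair arguments.

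- **The whole arm need not be exposed.** Part I runs for three months at all 18 sites, so many women may have consented before randomisation. A reader might infer from the f = 1 column that a bias of 2-6 points is to be expected. The documents do not support that: the share of new consenters is not given, and f = 1 supposes that no baseline consent carries over. This objection stands, and the range over f reflects it.
- **Baseline consent may already carry forward.** Sources of Materials says the abstraction form holds a study ID and the record number so that a woman's treatment and outcomes can be followed over time. The consent form itself is not available for review, so it cannot be said to lack this. This stands, and only a confirmation can be asked for.
- **The direction is not shown.** A reader might infer that the selection must favour integration. That needs consent to depend on use, and more strongly at intervention sites. Nothing in the Protocol says so. Consent is for abstraction only, unpaid, and the consent text mentions an interviewer, not clinic staff. This stands.
- **The coverage conflict is partly wording.** Encounter forms may be completed for everyone and abstracted only for consenters, and the sample size section speaks of recruiting. That explains the Endpoints phrase but does not make it correct.
- **The remedy is analysis-plan or reporting material.** The supportive analysis alone could wait for that plan. The consent log could not, because it cannot be rebuilt once collection is over. The main estimate would remain exposed to any such selection, but the log would show whether consent differed by arm.

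**Conclusion.** The point holds as a risk that the Protocol creates and answers wrongly. Endpoints and section 3.1 name a population that the consent section does not deliver. Women first consenting in months 7-15 enter after allocation to a visible arm. The reliance on randomisation under Potential Design Pitfalls does not reach behaviour that follows allocation.

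Size and direction are unknown. Under the stated assumptions the spurious difference runs from 0.5-1.4 points (a quarter consenting after allocation) through 1-3 points (half) to 2-6 points (all), and it is zero where consent is unrelated to use or equally related in both arms. Bias towards integration is plausible but not demonstrated. The required sample size is unaffected.

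**What to change.** 1. In Endpoints, replace the reference to all HIV-positive clients with consenting clients, and align section 3.1.
2. Confirm, in the Protocol text, that consent given in Part I covers abstraction through month 15.
3. At each site, log the women eligible, approached and consenting, with the date of consent. Report the proportions by arm, which respects the Protocol's rule against presenting results by facility.
4. Keep all consenting women as the main set, and prespecify a supportive analysis of contraceptive prevalence in women who consented before randomisation. That comparison is free of post-allocation consent selection.
5. Correct the statement under Potential Design Pitfalls: randomisation balances motivation that exists before allocation, not approach or consent behaviour that the arm changes.

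The cost is a tally sheet, one extra analysis and a few sentences. The supportive set leaves out clients who enrol after baseline, so it is smaller and describes a narrower population.
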